## Exclusion criteria:

[1] All patients who are not willing to be a part of study

[2] All patients with uncontrolled systemic diseases

[3] Small lesions of tongue for primary closure.

[4] Poland Syndrome

## Study procedure:

Procedure will be done at Siddharth Gupta Memorial Cancer Hospital (SGMCH), DMIHER, Sawangi, Wardha for patients presenting with non-
healing ulcers over the tongue.

[1] Patient Evaluation: Patients reporting to the Department of Oral and Maxillofacial Surgery will undergo a thorough examination.

[2] Case History: A detailed medical, dental and personal history will be documented.

[3] Clinical Examination: A comprehensive assessment of the oral cavity, focusing on the non-healing ulcer sites, will be conducted.

[4] Biopsy: A biopsy will be performed for histopathological examination to confirm the presence of squamous cell carcinoma.

[5] Radiographic Examination: Patients with confirmed squamous cell carcinoma will undergo a MRI to assess the extent of the lesion and 
detect any lymph node metastasis

This protocol ensures accurate diagnosis and appropriate management for patients presenting with suspected tongue cancer at SGMCH. After 
diagnosis, patients will be divided into two groups by computer generated randomization and undergo surgery under all aseptic protocols. 
After surgery, the patient will be monitored and after 1 week, 3 months and 6 months, they will be evaluated for functional and aesthetic 
outcomes, according to which the PMMC and PMMF flap will be judged. The two groups will be divided based on the type of reconstruction to 
be done after wide local excision or composite resection of the lesion and suitable neck dissection, which are 1) Group I - Reconstruction 
of surgical defect in squamous cell carcinoma of tongue with pectoralis major myocutaneous flap 2) Group II- Reconstruction of surgical 
defect in squamous cell carcinoma of tongue with pectoralis major myofascial flap. Once a pre-surgical workup has been completed, which 
includes pre-anaesthetic fitness, signed, showed and fully stated consents. After this pre-operative photos will be taken and the surgery 
will be performed. The conical assessment of the outcomes of the two types of reconstruction held would be done on the basis of the functional 
and aesthetic outcomes of the procedures post-operatively after 7 days, 1 month and 3 months of follow-up, which would help in keeping a 
close eye on the progress of the patients.

## Primary outcomes: 

Suture line leakage, Fistula, Flap discoloration and Donor site morbidity.

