myofascial (PMMF) flap a practical alternative for large oral cavity defects [18]. One major drawback 
of the PMMC flap is its bulk, which is influenced by the subcutaneous fat overlying the muscle and can hinder speech and swallowing 
rehabilitation, especially in anterior oral cavity and pharyngeal sites. This issue is more problematic in female or broad-chested patients 
and complications may be worsened when the mandible is preserved. Other limitations include intraoral hair growth, chest wall deformities 
and technical challenges with pedicle rotation. The PMMF flap, consisting of the pectoralis muscle and fascia without a skin island, addresses 
many of these drawbacks and has been reported as a versatile reconstructive option, although it remains underrepresented in the literature 
[19]. Partial hypopharyngeal defects following total laryngectomy (TLE) also pose reconstructive 
challenges. Loss of speech, impaired swallowing and complications such as fistulas, especially in previously irradiated patients, demand 
tailored approaches to optimize outcomes. While many techniques use free or regional flaps to create a cutaneous lining, the PMMC flap has 
lost favor because of its bulk and poor pliability. To overcome these issues, Robertson and Robinson introduced the PMMF flap in the 1980s, 
reducing complications. However, comparative evidence between PMMC and PMMF flaps remains limited [20]. 
Our study evaluates the post-operative outcomes of both flaps in tongue reconstruction. Most reconstructive techniques involve inverting a 
myocutaneous or fasciocutaneous free flap onto the remaining pharyngeal mucosa, forming a cutaneous lining. Historically, the pectoralis 
major myocutaneous (PMMC) flap has been widely used, but its bulkiness, poor pliability and risk of complications have reduced its 
popularity. To address these issues, Robertson and Robinson proposed the pectoralis major myofascial (PMMF) flap in the 1980s, which 
eliminates the skin island and reduces complications. Despite promising results, comparative studies between PMMC and PMMF flaps remain 
limited [20]. Therefore, this study aims to compare and evaluate the functional and aesthetic 
outcomes of the Pectoralis Major Myocutaneous (PMMC) flap versus the Pectoralis Major Myofascial (PMMF) flap for Type III and Type IV 
tongue defect reconstruction in patients operated on for squamous cell carcinoma of the tongue. Oral squamous cell carcinoma (OSCC) 

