viral infections and lifestyle-related influences. These findings highlight the importance of further research to identify nontraditional 
risk factors and improve prevention and early diagnosis strategies for younger populations affected by TSCC [8]. 
Oral cavity and pharyngeal cancers continue to contribute significantly to the global cancer burden, with higher incidence rates reported 
in men than in women. Management of oral tongue cancer requires a multidisciplinary approach involving oncologists, speech therapists, 
rehabilitation specialists and psychological support to address the complex functional and aesthetic challenges associated with treatment 
[15]. In reconstructive management following ablative surgery for oral squamous cell carcinoma, both 
Pectoralis Major Myocutaneous (PMMC) flaps and free flaps have demonstrated comparable complication rates. Although free flaps offer 
superior versatility and functional outcomes, PMMC flaps remain a practical and cost-effective option in resource-limited settings, 
particularly where financial constraints, lack of microvascular facilities and patient comorbidities limit the use of free flap 
reconstruction. Therefore, PMMC reconstruction continues to maintain clinical relevance in developing healthcare systems [16]. 
Therefore, it is of interest to compare the functional and aesthetic outcomes of pectoralis major myocutaneous and pectoralis major 
myofascial flaps for reconstruction of Type III and Type IV tongue defects following surgical treatment of tongue squamous cell carcinoma.

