## Secondary outcomes: 

Aesthetic outcomes, including flap shape and size, along with functional outcomes such as swallowing ability, speech and tongue mobility, 
will be evaluated (Table 1, Table 2, Table 3,
Table 4).

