## Statistical analysis:

Following data collection, data will be entered into Microsoft excel worksheet (Microsoft, USA). Data analysis will done using IBM 
Statistical Package for Social Sciences (Statistics for Windows, Version 21.0. Armonk, NY: IBM Corp.) Categorical data will be described in 
terms of frequencies and percentages. Continuous data will be presented by mean and standard deviation (SD). Comparison of means to assess 
functional and aesthetic outcomes in reconstruction of Type III and Type IV Tongue defects with Pectoralis Major Myocutaneous Flap VS 
Pectoralis Major Myofascial Flap in patients being operated for squamous cell carcinoma of tongue will be done using Repeated Measures 
ANOVA and unpaired 't' test. For categorical data, chi square test will be used to compare the proportions. For analysis, p-value less than 
0.05 will be considered statistically significant.

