## Expected outcome:

The present protocol is expected to determine whether PMMF flap reconstruction provides superior functional rehabilitation, improved 
speech and swallowing outcomes and reduced donor site morbidity compared to PMMC flap reconstruction in Type III and Type IV tongue defects.

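### The flaps are to be judged on function and aesthetics, but the primary outcomes are four unranked complications, so the primary analysis answers only the complication part of the purpose and any one of four tests could be declared positive

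*Protocol article*

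**What the plan says.** **Aim.** The Background gives the purpose twice in the same terms: "Therefore, this study aims to compare and evaluate the functional and aesthetic" outcomes of the two flaps, and again "Therefore, it is of interest to compare the functional and aesthetic outcomes of pectoralis major myocutaneous and pectoralis major" myofascial flaps. The Study procedure section makes this the decision basis. Patients are evaluated at follow-up for functional and aesthetic "outcomes, according to which the PMMC and PMMF flap will be judged".

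**Primary outcomes.** The whole section reads "Suture line leakage, Fistula, Flap discoloration and Donor site morbidity". It gives no order, composite or rule for combining the four.

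**Secondary outcomes.** "Aesthetic outcomes, including flap shape and size, along with functional outcomes such as swallowing ability, speech and tongue mobility" are placed here, scored on the five-point scales of Tables 1 to 4.

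**Analysis.** Under Statistical analysis, "For categorical data, chi square test will be used to compare the proportions", and for all analyses a p-value below "0.05 will be considered statistically significant".

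**Sample size.** Cochran's formula is applied to a 2% rate of total flap necrosis, giving 12 per group and 24 in total. Total flap necrosis is listed under neither the primary nor the secondary outcomes.

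**The concern.** The label of primary outcome decides which result the trial stands on. Here it sits on four complications, while the outcomes by which the flaps are to be compared carry the lower rank. The primary result could favour one flap because of, say, flap discoloration and say nothing about speech, swallowing or mobility. The functional conclusion that the authors anticipate would then rest on unranked secondary tests.

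The article also does not say what counts as success on the primary outcomes. With four tests, one threshold and no joint rule, a single p<0.05 could be called a positive trial. Two complications pointing in opposite directions could not be resolved.

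**Working it through.** **1. The plan's own figure.** Inputs from the sample size section: z = 1.96, p = 0.02, e = 0.08.

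n = z² × p × (1 − p) / e² = 3.8416 × 0.02 × 0.98 / 0.0064 = 11.76, so 12 per group and 24 in total. This reproduces. It is a precision calculation for one proportion and contains no alpha, power or difference between arms, so it gives no basis for any of the four primary outcomes or for the functional scales.

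**2. The sections side by side.**

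| Where | What it points to |
|---|---|
| Background (twice) | Function and aesthetics |
| Study procedure, basis for judging | Function and aesthetics |
| Primary outcomes | Four complications |
| Secondary outcomes | Function and aesthetics |
| Sample size | Total flap necrosis |

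The outcomes that decide between the flaps are not the primary ones.

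**3. Nominal false-positive rate.** With four independent tests, each at exactly 0.05: 1 − 0.95⁴ = 0.1855, or 18.5%. Under any dependence the bound is 4 × 0.05 = 20%, provided each test holds 5%.

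**4. Actual rate at 12 versus 12.** Chi-square on small counts does not hold exactly 5%. Assume each complication is recorded as yes or no once per patient, both arms share a true rate p, and the four outcomes are independent. The size of one test is

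s(p) = Σₐ Σ_b Bin(a; 12, p) × Bin(b; 12, p) × 1[test significant for a/12 versus b/12],

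and the chance of at least one false positive in four is 1 − (1 − s)⁴. The article gives no event rates for these outcomes, so p is varied.

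| Assumed rate p | s, uncorrected chi-square | Four tests | s, Fisher or continuity-corrected | Four tests |
|---|---|---|---|---|
| 5% | 0.0024 | 1.0% | 0.0002 | 0.1% |
| 10% | 0.0149 | 5.8% | 0.0025 | 1.0% |
| 20% | 0.0387 | 14.6% | 0.0119 | 4.7% |
| 30% | 0.0492 | 18.3% | 0.0172 | 6.7% |
| 40% | 0.0594 | 21.7% | 0.0210 | 8.1% |
| 50% | 0.0640 | 23.3% | 0.0228 | 8.8% |

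**5. After a fix.** One primary test at 0.05 has a nominal rate of 5%. Four tests at 0.05/4 = 0.0125 give 1 − 0.9875⁴ = 4.9% if independent, and at most 5%.

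**6. What 0.0125 demands.** For 0/12 versus 5/12 the uncorrected chi-square is 24 × (12 × 5)² / (12 × 12 × 5 × 19) = 86,400 / 13,680 = 6.32, p = 0.012, which passes. By Fisher, 0/12 versus 6/12 gives p = 0.0137, which fails, and 0/12 versus 7/12 gives p = 0.0046, which passes.

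**The case against.** **Complications belong to the study's purpose.** The Abstract lists flap-related complications among the outcomes. The Expected outcome section begins "The present protocol is expected to determine whether PMMF flap reconstruction provides superior functional rehabilitation, improved" speech and swallowing, and then adds less donor site morbidity, which is one of the four primaries. The Conclusion looks for fewer complications after surgery. This stands. A reader might infer that the primary analysis misses the question altogether, but these sections do not support that: it answers part of it. They do not, however, reconcile the primary outcomes with the Study procedure section, which judges the flaps on function and aesthetics.

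**The error rate may be small.** This also stands. A reader might take 19% as the false-positive rate, or as its ceiling. It is neither. It is the nominal figure for independent tests that each hold 5%. If complications are uncommon the rate is far lower, and if they are common and chi-square is uncorrected it is somewhat higher.

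**Repeated visits.** A reader might multiply the tests by the three follow-up visits and arrive at a much larger rate. The article does not say that complications are tested visit by visit, and for the scales it names repeated measures ANOVA as well as the t test. No such figure is supported.

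**A separate analysis plan could add a multiplicity rule.** It could. It could not make the primary outcomes match the aim, because the protocol itself fixes which outcomes are primary.

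**Conclusion.** The point holds as a contradiction within the protocol: stated aim and decision basis on one side, rank of the outcomes on the other. This conclusion needs no assumption about event rates and would stand even if the error inflation proved negligible.

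The false-positive part is secondary and uncertain in size. It is 18.5% nominally, about 1% to 23% by exact calculation with uncorrected chi-square for assumed event rates of 5% to 50%, and below 9% with Fisher or a continuity correction. These figures assume independent outcomes, equal true rates in the two arms, one yes/no record per patient for each complication, and 12 analysed patients per arm.

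**What to change.** Make the change before anyone sees outcome data by arm. The article dates the study from February 2025, so recruitment may already have begun, and a later choice would be open to the charge of being data-driven. Either route reconciles the sections.

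**Route 1: match the primary to the aim.** Name one functional score already collected (for example swallowing, Table 2) at one named visit as the single primary outcome, at two-sided 0.05. Make the four complications secondary, each counted once per patient over follow-up. The named visit first requires reconciling the two schedules in the Study procedure section: 1 week, 3 months and 6 months in one place; 7 days, 1 month and 3 months in another.

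**Route 2: keep complications primary.** Use one composite (any listed complication by the last visit), or Holm across the four at an overall 0.05, and restate the aim to match.

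**Cost.** Amendment wording only, with no new data. Under Route 1 complications lose stand-alone primary status. Under Holm the first test needs p<0.0125, which means 0/12 versus 5/12 by uncorrected chi-square or 0/12 versus 7/12 by Fisher; the test should be named. Under either route the article should state that 24 patients were not sized for the chosen primary. For a functional score compared by t test, 80% power at 12 per arm needs a difference of about (1.96 + 0.84) × √(2/12) = 1.14 SD by the normal approximation, or about 1.2 SD allowing for the t distribution.

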## Secondary outcomes: 

Aesthetic outcomes, including flap shape and size, along with functional outcomes such as swallowing ability, speech and tongue mobility, 
will be evaluated (Table 1, Table 2, Table 3,
Table 4).

## Statistical analysis:

Following data collection, data will be entered into Microsoft excel worksheet (Microsoft, USA). Data analysis will done using IBM 
Statistical Package for Social Sciences (Statistics for Windows, Version 21.0. Armonk, NY: IBM Corp.) Categorical data will be described in 
terms of frequencies and percentages. Continuous data will be presented by mean and standard deviation (SD). Comparison of means to assess 
functional and aesthetic outcomes in reconstruction of Type III and Type IV Tongue defects with Pectoralis Major Myocutaneous Flap VS 
Pectoralis Major Myofascial Flap in patients being operated for squamous cell carcinoma of tongue will be done using Repeated Measures 
ANOVA and unpaired 't' test. For categorical data, chi square test will be used to compare the proportions. For analysis, p-value less than 
0.05 will be considered statistically significant.

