## Inclusion criteria:

[1] All the patients age 18 years and above with Biopsy proven case of Squamous Cell Carcinoma of Tongue

[2] Type III and Type IV Tongue defects according to Ansari classification

[3] Patients fit to undergo surgery ASAI

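### The four five-level scores are compared by unadjusted t-tests and repeated measures ANOVA at 0.05, with no deciding test, term or visit and without the Type III/IV defect class

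*Protocol article*

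**What the plan says.** All references are to the Protocol article.

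- **Outcomes.** The Secondary outcomes section lists "Aesthetic outcomes, including flap shape and size, along with functional outcomes such as swallowing ability, speech and tongue mobility". Tables 1 to 4 give the instruments: tongue shape, swallowing, speech and tongue mobility, each an ordered grade scored 1 to 5.
- **Analysis.** The Statistical analysis section plans a comparison of means that "in patients being operated for squamous cell carcinoma of tongue will be done using Repeated Measures" "ANOVA and unpaired 't' test". Data that it calls continuous are summarised by mean and SD. For other data, "For categorical data, chi square test will be used to compare the proportions". The threshold is that a p-value below "0.05 will be considered statistically significant".
- **Defect class.** The Inclusion criteria admit "Type III and Type IV Tongue defects according to" a named classification. The Statistical analysis section mentions both types when it describes the comparison, but names no covariate. Neither the Sample size calculation nor the Study procedure section, which describe the randomisation, names a stratification factor.
- **Visits.** The Abstract and the end of the Study procedure section give 7 days, 1 month and 3 months. Earlier, the Study procedure section gives 1 week, 3 months and 6 months.

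**The concern.** Two methods are named for the same scores, and nothing says which one settles the question. A repeated measures ANOVA itself yields a group main effect and a group-by-visit term, which respond to different patterns of benefit. A t-test can be run at any visit. With 12 patients per arm, the conclusion may depend on which of these is read, and each is allowed its own 0.05.

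The scores are labelled secondary, but the Utility, Expected outcome and Conclusion sections rest much of the trial's message on them: better speech, swallowing, mobility and functional recovery. The rule for claiming that benefit therefore matters.

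The plan also leaves out the one patient characteristic that its own eligibility rule already requires to be known. If Type III and Type IV defects differ in function, that difference stays in the residual variance, and a chance imbalance between the arms goes uncorrected.

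**Working it through.** **Inputs from the Protocol article.** 12 per arm and 24 in total; four scales; three visits; alpha 0.05. Sidedness is not stated, so two-sided is assumed. The article gives no effect size, SD, visit correlation or dropout rate for these scores. Those values below are assumptions, shown as ranges where they were varied.

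**1. The plan's own figure.** n = z²p(1−p)/e² = 1.96² × 0.02 × 0.98 / 0.08² = 11.76, rounded up to 12 per group. This reproduces the stated figure. It rests on flap necrosis and says nothing about the scores, so it neither supports nor limits their analysis.

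**2. Number of tests.** On the reading that t-tests are run at every visit, there are 4 × 3 = 12.
- Independent tests: 1 − 0.95¹² = 0.46.
- Correlated tests (simulation, 2,000 null trials per setting): 0.39, 0.36 and 0.28 for between-scale/between-visit correlations of 0.3/0.5, 0.5/0.5 and 0.7/0.7.
- Adding the two ANOVA terms for each scale: 0.46, 0.42 and 0.34 for the same settings.
- One contrast per scale: 1 − 0.95⁴ = 0.185 if independent. Testing each at 0.05/4 = 0.0125 keeps the total at or below 0.05.

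**3. Which term is read.** Simulated power with 12 per arm, normal scores and SD 1 (3,000 trials per setting). The ranges cover visit correlations of 0.3 to 0.7.

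| True arm difference over the three visits (SD) | Group main effect | Group-by-visit | Last-visit t-test |
|---|---|---|---|
| 0, 0, 1 | 0.14–0.19 | 0.51–0.89 | 0.64–0.65 |
| 0, 0.5, 1 | 0.26–0.35 | 0.40–0.78 | 0.65 |
| 1, 1, 1 | 0.76–0.90 | 0.04–0.05 | 0.66 |

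No column is best throughout, so the choice has to be fixed in advance.

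**4. Defect type.** Power of a single-visit comparison for a 1 SD arm effect, with each patient equally likely to be Type III or IV (3,000 trials per setting):

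| Difference between types (SD) | Unadjusted | Adjusted |
|---|---|---|
| 0 | 0.65 | 0.63 |
| 0.5 | 0.62 | 0.62 |
| 1.0 | 0.56 | 0.62 |
| 1.5 | 0.46 | 0.62 |

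A second simulation used scores rounded and clipped to 1–5, with between-patient SD 0.8 and residual SD 0.6. The total is √(0.64 + 0.36) = 1.0, so one point is about one SD before rounding. Last-visit power rose from 52% to 58% when the types differed by 1 point (+6), and from 42% to 57% when they differed by 1.5 (+15). For a constant arm effect and a 1-point difference between types, adjustment also raised the power of the ANOVA main effect, from 0.62 to 0.73.

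Imbalance: if 12 of the 24 patients are Type IV (assumed), the hypergeometric chance that the arms differ by four or more Type IV patients is 0.22.

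**5. Missed visits.** A classical repeated measures ANOVA uses only patients seen at every visit. If a share m miss each visit independently, 24(1 − m)³ remain: 20.6 at 5%, 17.5 at 10%, 14.7 at 15% and 12.3 at 20%. For a 1 SD difference at one visit, t-test power is 0.65 with 12 per arm and 0.51 with 9.

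**6. Five-level scores in a t-test.** With 12 per arm and three assumed distributions over the grades (20,000 trials each), the type I error was 0.053, 0.048 and 0.044.

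**The case against.** Much of a harsher criticism would not stand.

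- **Late effects.** A reader might infer that the repeated measures ANOVA averages away a late benefit. That is true only of its group main effect, and the article does not say that this term is the one read. The group-by-visit term, or the t-test that the article also names, would pick up a late effect. For a constant effect the main effect is the strongest test.
- **Size of the gain.** Setting the main effect against an adjusted last-visit test, under an effect that grows over time, suggests that the planned power is more than doubled. That is not a fair comparison, because the plan already names a t-test. Against the same visit unadjusted, the gain is the 6 or 15 points in step 4. Nothing in the article shows that the effect grows; the Background attributes the speech and swallowing drawback of the myocutaneous flap to its bulk.
- **Ordinal scores.** A reader might infer that t-tests on 1–5 grades are invalid. Step 6 shows error close to 5%, so a different summary is a preference.
- **Lost patients and test count.** The article states no dropout rate, and a missing-data rule or a multiplicity rule for secondary outcomes may sit in an analysis plan that is not shown. It does not say that t-tests are run at every visit, so 12 is one reading.
- **Defect type.** The article does not say that the class drives function. The actual defect is created by the resection, after randomisation, so adjusting for the class found at surgery could mean adjusting for a post-randomisation variable.

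These points limit the size of the finding. They leave intact what the Statistical analysis section does state: two unadjusted methods for the same scores, each at 0.05, with no deciding test, term or visit. The last objection is met by using the class planned before randomisation.

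**Conclusion.** The point holds in a limited form. The plan leaves open which result decides and omits defect class. A better analysis is available from the same patients and in the software already named.

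The false-positive figures (0.46 if independent, about 0.28 to 0.39 with correlation) apply if t-tests are run at all three visits. The gain from adjustment, about 6 points of power for a 1-point difference between types and about 15 for 1.5, rests on assumed values. The loss to 17.5 of 24 patients rests on an assumed 10% missing per visit. The methods named are not invalid, and the documents do not show that a late effect would be missed.

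The final visit has no single meaning until the two schedules in the Study procedure section are reconciled.

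**What to change.** 1. Reconcile the two visit schedules in the Study procedure section.
2. For each scale, replace the t-tests and ANOVA by one linear mixed model (MIXED in SPSS) on all available visits, with arm, visit, arm-by-visit and defect type (III/IV) as planned before randomisation.
3. Report one prespecified arm contrast per scale with its 95% CI, for example at 3 months, the later time point that both schedules contain.
4. Name one lead scale, or test the four at 0.05/4 = 0.0125. Label any per-visit t-tests descriptive.
5. Do not use an ordinal logistic GEE with 24 patients unless a small-sample correction is applied. In a null simulation with uncorrected sandwich errors it rejected 8.7% of the time at the last visit. That came from only 298 converged fits, so the standard error is √(0.087 × 0.913 / 298) = 1.6 points.

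The cost is a rewrite of one sentence and a record of the planned defect class before randomisation. The sample size does not change. There are two downsides. Adjustment loses about 2 points of power if defect type has no effect. A single-visit contrast is also weaker than the average over visits if the flap effect is constant over time: about 0.60 to 0.62 against 0.75 in a simulation with no defect-type effect. If a constant effect is thought more likely, the average over visits from the same model can be prespecified instead, provided that one contrast is fixed in advance.
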